### Sample size calculation

For non-inferiority, we assume that the intervention group should have an average decrease in Kmax of 1.0 D, based on clinical experience and recent evidence. The non-inferiority margin is equal to -0.3 D (i.e., the mean difference between cCXL and sCXL should be greater than -0.3 to achieve statistical significance). Assuming this non-inferiority margin and a within-group standard deviation (SD) of 1.72 D, we need to include 55 patients per group to detect non-inferiority with 90% power and a one-sided significance level alpha of 0.025. The sample size was calculated using an online calculator for the comparison of two means (www.powerandsamplesize.com). Accounting for 10% loss-to-follow-up, we need to include 62 patients per group, i.e., 124 patients in total.

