In 2003 Wollensak et al. introduced corneal crosslinking (CXL) to halt the progression of keratoconus in humans [11]. First the top layer of the cornea, the epithelium, is debrided after which the cornea is soaked for 30 min with the photosensitizer riboflavin. Hereafter a 9.0 mm diameter Ultraviolet-A (UV-A) beam radiates the cornea for 30 min with a fluence of 3 mW/cm^2^ resulting in a total energy of 5.4 J/cm^2^. This protocol is called the Dresden protocol. Currently, accelerated versions of the Dresden protocol are used in clinical practice with different fluences of 9mW/cm^2^, 10mW/cm^2^ and 15 mW/cm^2^. The higher the fluence, the shorter the treatment time, in which, according to the Bunsen–Roscoe reciprocity law, the total amount of energy stays the same [12–14]. During the corneal crosslinking oxygen radicals are formed that interact with the surrounding molecules, leading to the formation of new chemical bounds between the collagen fibrils (i.e. corneal crosslinks) [15], with the final goal to stiffen the cornea and halt the progression of the disease.

For any treatment, it is desirable that unaffected regions of the tissue involved are not unnecessarily treated by an intervention or drug application. To minimize the risk of damage to surrounding tissues in CXL it would be beneficial that the UVA beam is restricted only to the affected, keratoconic zone in the patient’s cornea [16]. This can be achieved by *customizing* the beam shape and size in a way that only the degenerated zone is treated, i.e., by customized crosslinking (*c*CXL). Recently, studies provided clinical evidence that similar clinical outcomes can be achieved if only the cone is treated rather than the whole cornea [17–20]. We hypothesized based on the results of these previous studies that only treating the affected zone has three potential benefits: (1) a faster recovery (e.g. increased corneal reepithelialisation), (2) stronger flattening of maximum keratometry and (3) better visual outcome (corrected distance visual acuity, CDVA). However, since none of these studies were randomized and study results were limited by small sample sizes, there is a need for a randomized controlled trial with an appropriate design and sample size to confirm these findings. This study will be setup as such, with the aim to investigate whether *c*CXL is non-inferior to *s*CXL in terms of halting the disease progression and flattening of the corneal surface.

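### The 55 patients per group for 90% power do not follow from the stated inputs; if the two techniques are equal, power is about 15%

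*Protocol article*

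**What the plan says.** All planning figures are in the section Sample size calculation of the protocol article.

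- Margin: "The non-inferiority margin is equal to -0.3 D", with the explanation that "the mean difference between cCXL and sCXL should be greater than -0.3 to achieve statistical significance".
- Variability: "a within-group standard deviation (SD) of 1.72 D".
- Planning mean: "we assume that the intervention group should have an average decrease in Kmax of 1.0 D". This is the only mean given. No expected change is stated for the sCXL arm, and no expected difference between the arms.
- Result, with error rate and power: "we need to include 55 patients per group to detect non-inferiority with 90% power and a one-sided significance level alpha of 0.025". It was obtained with an online calculator for comparing two means and raised to 62 per group (124 in total) for 10% loss to follow-up.

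The sentence with the result presents the 55 as the consequence of the margin and the SD. Elsewhere, the Background lists "stronger flattening of maximum keratometry" among the hypothesised benefits of treating only the affected zone, and the Discussion repeats this. Neither section attaches a figure to it.

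**The concern.** A non-inferiority trial is usually sized on the assumption that the treatments are equal, or on a stated expected difference. The article states neither. A margin of 0.3 D is small against an SD of 1.72 D (a standardised distance of 0.3/1.72 = 0.17), and 55 per group is far too few to resolve that distance at 90% power.

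What is at stake is the meaning of the primary result. A reader who sees 90% power will expect the trial to succeed if cCXL is as good as sCXL. On the printed inputs it would more often end without an answer.

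**Working it through.** **Inputs** (all from Sample size calculation): margin 0.3 D; SD 1.72 D; one-sided alpha 0.025 (z = 1.960); power 90% (z = 1.2816); equal groups. The difference is taken so that a positive value favours cCXL, which is the direction in which the stated rule is a non-inferiority rule.

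**Formula.** With d the distance between the true difference and the margin (d = 0.3 + true cCXL advantage):

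n per group = 2 × [1.72 × (1.960 + 1.2816) / d]²

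**Step 1: try to reproduce 55.**

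| Reading | d (D) | n per group for 90% power | Power with 55 |
|---|---|---|---|
| Arms truly equal | 0.3 | 691 | 14.8% |
| 1.0 D minus the margin | 0.7 | 127 | 56.9% |
| 1.0 D as the distance from the margin | 1.0 | 63 | 86.2% |
| 1.0 D cCXL advantage plus the margin | 1.3 | 37 | 97.7% |

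None gives 55; the nearest is 63. At equality, other error rates do not help: one-sided 0.05 with 90% power needs 564, one-sided 0.025 with 80% needs 517, and one-sided 0.05 with 80% needs 407. A one-sample formula gives 346, 64, 32 and 19 at the four distances. Reading 1.72 as a variance gives 402 at equality. Two combinations come within two patients of 55, both at one-sided alpha 0.0125: 57 at 80% power with d = 1.0, and 53 at 95% power with d = 1.3. Both contradict the stated alpha and power.

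**Step 2: the loss-to-follow-up step.** 55 / 0.9 = 61.1, rounded up to 62. This step is correct. The same step applied to 691 gives 768 per group.

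**Step 3: what 55 would require.** Solving for d: d = 1.72 × 3.2415 × √(2/55) = 1.063 D. The implied true cCXL advantage is 1.063 − 0.3 = 0.763 D. Against a 1.0 D decrease with cCXL, that is an sCXL decrease of about 0.24 D. The implied advantage is about two and a half times the margin (0.763/0.3 = 2.5).

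**Step 4: power and precision with 55 per group.** SE = 1.72 × √(2/55) = 0.328 D. Power = Φ[(0.3 + true advantage)/0.328 − 1.960].

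| True cCXL advantage (D) | Power |
|---|---|
| 0 | 15% (14.6% by the noncentral t) |
| 0.25 | 39% |
| 0.5 | 68% |
| 0.76 | 90% |

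With all 62 per group retained, power at equality is 16%. The half-width of the 95% CI is 1.960 × 0.328 = 0.64 D, more than twice the margin. For the lower limit to clear −0.3 D, the observed cCXL advantage must be at least 0.64 − 0.30 = 0.34 D.

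**Step 5: can the mixed model close the gap?** The article gives no correlation, so a range is assumed. The residual SD is 1.72 × √(1 − ρ²).

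- ρ = 0.5: residual SD 1.49 D, SE 0.284 D, power at equality 18%, required observed advantage 0.26 D.
- ρ = 0.7: residual SD 1.23 D, SE 0.234 D, power at equality 25%, required observed advantage 0.16 D.
- For 90% power at equality the residual SD would have to be 0.3 / (3.2415 × √(2/55)) = 0.485 D. That needs ρ of about 0.96, or 92% of the variance explained.

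**The case against.** The strongest reply is that the article never says the arms are assumed equal. It names a planning mean for the cCXL arm, and the Background and Discussion expect more flattening with cCXL. If an sCXL decrease near 0.24 D was entered in the calculator, 55 per group does give 90% power, and the full protocol may record that entry. This stands in part. The 15% is the power under equality, not the power of the trial whatever the truth. The reply does not rescue the paragraph, though: the article prints margin, SD, alpha, power and result as one complete calculation, and the input that would make it work is not among them.

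A reader might then infer that the authors did plan on a 0.76 D advantage and left it out. The documents do not support that. The 0.76 D is derived from n = 55 and appears nowhere in the text; an error in entering the inputs would explain the 55 equally well.

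A second reply is that the linear mixed model in Statistical analysis uses repeated measures, the Kmax stratum and covariates, and so gains precision. That is fair, and the 0.34 D requirement and the roughly 85% chance of failure at equality therefore hold only for an unadjusted SD of 1.72 D with 55 per group. Over the assumed range of correlations, however, power at equality stays at or below about 25%, and the article claims no gain of this kind in its calculation.

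It is also tempting to predict that a failed non-inferiority test would be misread as evidence against cCXL. Nothing in the article says how such a result would be interpreted, so that is not part of this point.

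**Conclusion.** The point holds as a wrong figure in the primary power calculation: 55 per group at 90% power cannot be obtained from the stated margin, SD and alpha under any reading of the 1.0 D tried. If the techniques are equal, the requirement is 691 per group, and 55 gives about 15% power unadjusted, or about 18-25% if adjustment achieves a correlation of 0.5 to 0.7 (an assumption). Ninety per cent is reached only at a true cCXL advantage of about 0.76 D.

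Two limits apply. The documents cannot show whether such an advantage was assumed or the 55 is a mistake. And the 691 is the consequence of assuming equality, not a finding that the trial must recruit that number. The figures rest on a two-sample comparison of means with a common SD of 1.72 D and equal groups.

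**What to change.** Restate the sample size paragraph; no extra patients are required.

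1. Give the sCXL mean and the between-arm difference actually entered in the calculator, with their source. If none was entered, correct the power claim. The back-solved 0.76 D should not be adopted afterwards as though it had been the planning value.
2. Report power for 55 per group over plausible true differences: about 15% at 0 D, 39% at 0.25 D, 68% at 0.5 D and 90% at 0.76 D. If a gain from covariate adjustment is claimed, state the assumed correlation.
3. State that, on the planning SD, the 95% CI half-width is about 0.64 D, so an observed cCXL advantage of about 0.34 D is needed, and that failure to show non-inferiority is inconclusive.

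Optionally, a superiority test of the same 12-month contrast could be pre-specified in fixed sequence after non-inferiority, at no cost in alpha. It is not needed to correct the error.

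The cost is a rewritten paragraph and a much less favourable power statement.

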### Randomisation and blinding

Participants of the study will be randomized to either cCXL or sCXL (control), after applying the stratification factor of ‘Kmax < 58D’ or ‘Kmax ≥ 58D’. Each patient will receive a randomization number from a computerized random number generator. In Castor EDC, the subject number will be linked to one of the treatment arms (either cCXL or sCXL) through block randomization. Random varying block sizes of 2 and 4 will be used. The randomization procedure will be done by the principal investigator.

Since it is clear to both patients and surgeons which intervention will be performed, blinding will not be possible. The investigator that performs postoperative examinations will be blinded. Potential deblinding will be logged in the case report form (CRF).

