### Study population

Patients will be included from the outpatient ophthalmology department at the three academic centres. Inclusion criteria are patients between the age of 16 and 45 years old with progressive keratoconus based on one or more of the following changes within 12 months: 1 dioptre (D) increase in keratometry (Kmax, K1, K2) or 10% decrease of corneal thickness or 1 D increase in myopia or refractive astigmatism. Exclusion criteria are corneal scarring, corneal diseases other than keratoconus, history of corneal surgery (e.g. refractive surgery, corneal transplantation, intracorneal ring segments), unwilling or unable to give informed consent, unwilling to accept randomization or inability to complete follow-up (e.g. hospital visits) or comply with study procedures, insufficient corneal thickness including epithelium < 400 µm, pregnancy, if both eyes are eligible only the first eye which is undergoing corneal crosslinking is enrolled in the study, or participation in another clinical study.

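### Published blocks of 2 and 4 in an open trial make allocations easy to guess for anyone who sees a stratum's history, and the protocol does not settle who sees it

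*Protocol article*

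**What the plan says.** All the design facts are in the protocol article, mostly under Randomisation and blinding.

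- Block sizes and who randomises: "Random varying block sizes of 2 and 4 will be used. The randomization procedure will be done by the principal investigator".
- Open treatment: "Since it is clear to both patients and surgeons which intervention will be performed, blinding will not be possible".
- Outcome assessment: "The investigator that performs postoperative examinations will be blinded".
- Stratification: patients are randomised "after applying the stratification factor of" Kmax below 58 D or 58 D and above. Centre is not named as a factor.
- System: "In Castor EDC, the subject number will be linked to one of the treatment arms".

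Two other sections bear on who can see what. Study population says: "Patients will be included from the outpatient ophthalmology department at the three academic centres". Data management and monitoring refers to a principal investigator at each centre, so the single principal investigator named for randomisation could be one person or three.

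**The concern.** In an open trial each allocation becomes known once the patient is treated. Permuted blocks force the arms back to equality at the end of every block. Blocks of 2 and 4 do this so often that the running difference between the arms says a good deal about the next allocation. Varying the size between 2 and 4 hides little, because both sizes return to balance quickly. The article also prints the sizes.

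Someone who can predict the next arm and also influences enrolment can, even unintentionally, bring patients forward, delay them or leave them out according to expected outcome. This is selection at entry. Blinding the postoperative examiner and measuring Kmax with the Pentacam limit detection bias, but neither acts on who enters which arm. The mixed model adjusts for the Kmax stratum and for recorded variables related to outcome. It cannot adjust for an unrecorded clinical impression of the patient.

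**Working it through.** The protocol gives no figure for predictability, so there is none to reproduce.

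**Inputs from the protocol.** Block sizes 2 and 4, two arms, two Kmax strata, three centres, 124 patients, open treatment.

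**Assumptions.** The two sizes are equally likely; the article does not give the chances, so the chance of a block of 2 is varied from 1/3 to 2/3. The observer names the arm that is behind in the stratum and tosses a coin when the arms are level. Every block ends level, so block boundaries are not needed for this rule.

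**1. Correct guesses, full view of the stratum**

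- Block of 2: the expected number correct is 0.5 + 1 = 1.5, or 1.5/2 = 75.0%.
- Block of 4: by position, 0.5 + 2/3 + (2/3 × 0.5 + 1/3 × 1) + 1 = 2.833, or 2.833/4 = 70.8%.
- Both sizes equally often: (1.5 + 2.833)/(2 + 4) = 72.2%, against 50% by chance.
- Chance of a block of 2 from 1/3 to 2/3: 71.7% to 72.9%.

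**2. How good the guess is when the arms are unequal**

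- The arms are unequal before 1 allocation in a block of 2 and before 1 + 1/3 + 1 = 2.333 in a block of 4. The share is (1 + 2.333)/6 = 55.6%.
- The guess is then right for 1 and for 2/3 + 1/3 + 1 = 2 allocations respectively: 3/3.333 = 90%.

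**3. Allocations known with certainty, block boundaries unknown**

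- A difference of 2 between the arms can arise only when a block of 4 opens with two equal allocations, which has probability 1/3. It then fixes the next two.
- Share: (0.5 × 1/3 × 2)/3 = 1/9 = 11.1%, where 3 is the mean block length. This is 0.111 × 124 = 13.8 patients.
- Simulated lists of 62, where the last block may be cut short, give 10.9%, or 0.109 × 124 = 13.5.
- Chance of a block of 2 from 1/3 to 2/3: 13.3% to 8.3%.

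**4. View of one centre only, list shared by three centres**

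This was simulated with 124 patients and two strata. The observer names the arm that is behind among local patients in the same stratum.

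| Split of patients over centres | Correct guesses |
|---|---|
| Equal thirds | 52.9% |
| 50/30/20 | 53.3% to 53.4% |
| 70/20/10 | 54.9% |

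If lists were kept separately per centre, which the article does not state, a local view would again give about 72%.

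**5. Larger blocks, full view of the stratum**

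| Block sizes | Guessed correctly | Known with certainty |
|---|---|---|
| 2, 4 | 72% | 11% (13 to 14 of 124) |
| 4, 6 | 69% | 5.6% (about 7 of 124) |
| 4, 6, 8 | 68% | 2.3% (about 3 of 124) |

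With blocks of 4, 6 and 8, the guess when the arms are unequal is right 78% of the time instead of 90%. For an observer who sees one of three equal centres on a shared list, correct guessing hardly changes (52.8% against 52.9%).

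**The case against.** The strongest objection concerns access. A reader might infer that the person who randomises sees the running balance in every stratum and so guesses 72% correctly. The article does not establish this. If each of the three centres' investigators draws from a shared list and sees only local patients, guessing is close to chance. If one investigator randomises for all centres, that person can see everything, but the article does not say that this person selects patients at the other two. Guessing becomes selection bias only where knowledge of the history and control over enrolment meet. This objection stands, and the size of the problem must be given as a range.

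Other strong readings also go too far.

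- **A run of three equal allocations fixes the next one.** It need not. After a block BBAA, a new block opening with A completes a run of three A's, yet the arms differ by only 1. The next allocation is again A with probability 0.5 × 1/3 = 1/6. Only a difference of 2 gives certainty.
- **All allocations that the block forces are known in advance.** By design 38.9% are forced, but recognising most of them requires the block boundaries, which random sizes usually hide.
- **No analysis could repair the damage.** The Statistical analysis section adjusts for the Kmax stratum and for variables related to outcome, so selection on those recorded factors is at least partly handled. Selection on unrecorded prognosis remains.
- **The absence of a described lock on eligibility and consent before release in Castor is a defect.** That is operational detail which a condensed article may omit, and nothing in the text says the next allocation is visible beforehand. Hiding it would not, however, prevent inference from past allocations.
- **Bias has occurred.** The documents show a risk. They give no evidence of bias and no direction for it.

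It is also fair to say that larger blocks lower overall guessing only modestly, and that few allocations may remain. The trial was registered in August 2020, the article appeared in May 2023, and the abstract speaks of inclusion in the past tense while the Methods use the future tense.

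**Conclusion.** The point holds as a conditional weakness in a design choice that the article itself fixes and publishes. For a person with full sight of a stratum, about 72% of allocations are guessable and about 11% are certain, assuming equal use of the two sizes; the 72% barely moves when that assumption is varied. For a person who sees one centre on a shared list, the figure is about 53% to 55%. Randomisation and blinding, read with Data management and monitoring, does not settle which case applies. The consequence at stake is selection at enrolment on prognosis outside the model. It is worth correcting because a better setting costs almost nothing.

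**What to change.** For all allocations still to be made:

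1. Drop block size 2 and use random blocks of 4, 6 and 8 in Castor. The main gain is in certain allocations, from 13 or 14 to about 3 of 124.
2. Do not disclose the new sizes to staff who enrol patients.
3. Have the allocation triggered by existing staff who do not select or enrol patients. If that is not feasible, at least keep the cross-centre allocation history from those who enrol. This step matters more than block size, since overall guessing with a full view falls only from about 72% to 68% with the larger blocks.
4. State whether the principal investigator who randomises is one person or one per centre, and which allocation history that person sees.

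The cost is a Castor setting, a reassigned task and a protocol note. The downside is a possible arm imbalance within a Kmax stratum of up to 4 (half of a block of 8) instead of 2 (half of a block of 4), which the stratum-adjusted model handles. If recruitment is already complete, only item 4 can still be done, in the report of the trial.

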### Data management and monitoring

Personal data will be managed confidentially, according to Good Clinical Practice guidelines. All essential documents, including informed consent forms, CRF, and questionnaires will be collected by the principal investigator of each study centre and will be stored in an investigator site file for a period of 15 years. CRFs will be documented electronically in Castor, by a member of the study team of each study centre. The Clinical Trial Centre Maastricht (CTCM) will monitor the study to protect patient rights and accuracy of reported trial data. The CTCM is an academic research organisation.

### Public disclosure and publication policy

The results of this study will be published in report form and scientific papers will be submitted for publication in appropriate journals in the international medical literature. The guidelines for public disclosure of WMO-studies, as stated by the Central Committee on Research Involving Human Subjects (CCMO) in their publication statement, will be followed. The results of this RCT will be reported according to the CONSORT (CONsolidated Standards Of Reporting Trials) statement.

### Data safety monitoring board

In this study a Data Safety Monitoring Board (DSMB) is established to perform ongoing safety surveillance and to perform interim analysis on the safety data, especially regarding the occurrence of an SAE. The DSMB is an independent committee of trial experts who will focus on safety monitoring, it consists of three members: two ophthalmologists and one member with a statistical/epidemiological background. The DSMB decides whether to recommend that the trial continues to recruit participants or whether recruitment should be terminated either for everyone or for some treatment groups and/or some participant subgroups. The DSMB may perform an interim analysis on safety, upon the suspicion of one of the treatments being more harmful than the other. Interim analyses on safety will be performed at least three times yearly. The advice(s) of the DSMB will only be sent to the coordinating investigators group of the study. Should the coordinating investigators group decide not to fully implement the advice of the DSMB, they will send the advice to the reviewing Medical Ethical Commission, including a note to substantiate why (part of) the advice of the DSMB will not be followed.

